### Physical Evaluation

Physical evaluation consists of body composition, physical function, and peak oxygen consumption assessment. Tests are performed in the morning between 9 AM and noon, and participants are asked not to participate in vigorous physical activity 24 hours before the tests.

Stature is measured with a stadiometer (Seca Bodymeter, Model 208, Germany) with a precision of 0.1 cm. Body composition (total body mass, fat mass, fat mass percentage, fat-free mass, and phase angle) is measured by bioimpedance (InBody 770; Biospace Co).

To measure the risk of falls and eligibility to perform our exercise programs, TUG, Chair Stand, and Hand Grip Strength tests are applied. TUG and Chair Stand tests are applied according to the Centers for Disease Control and Prevention STEADI guidelines [25,31]. Handgrip strength is measured with a hydraulic hand dynamometer (Lafayette, Model 5030 L1, USA). The strength of the dominant hand is tested in a standing position with straight arms. The test is repeated 3 times, and the best value of the 3 attempts is recorded [32].

Peak oxygen uptake capacity (VO_2_ peak) is measured with a submaximal incremental cycle ergometry test (Lode Excalibur, Netherlands). Following a warm-up period, participants start the testing phase with an initial load of 50 watts for women and 75 watts for men [33]. The load is increased by 25 watts at 3-minute intervals. The test is continued at 60 to 70 rpm and is completed once participants achieve 85% of their predicted maximal heart rate, as determined by the Tanaka formula [34].

### Blood Sample Collection and Analysis

To examine the effect of the intervention on inflammation and neuroprotection blood markers, blood samples are collected from venous blood (15 mL) in a fasting state in the morning by a registered nurse. A complete blood count is performed using a hematology analyzer (DXH500; Beckman Coulter, USA). Aliquots of plasma and serum samples are stored at −80 °C until further use.

Plasma samples will be quantified by enzyme-linked immunosorbent assay for interleukin (IL)-6, IL-1β, tumor necrosis factor-α, interferon-γ, IL-17, IL-1Ra, IL-10, irisin, and brain-derived neurotrophic factor (Thermo Fisher, UK), while serum samples will be analyzed for insulin growth factor 1, vascular endothelial growth factor, and glial cell line-derived neurotrophic factor (ElabScience, USA) according to the manufacturer’s instructions.

### Cognitive Assessment

General cognitive function is assessed using standardized neuropsychological tests (Table 3). Participants are screened for the presence of objective cognitive impairment using the Addenbrooke’s Cognitive Examination-Revised, which also incorporates the Mini-Mental State Examination, providing a double score [35], and for the presence of psychopathology using the Geriatric Depression Scale-30 [36,37]. Participants with objective cognitive deficits (according to the available norms) are excluded.

A comprehensive neuropsychological assessment protocol for detailed neurocognitive performance is performed for eligible participants with 4 tests from the Cambridge Neuropsychological Testing Automated Battery Connect Research system: Motor Screening Task, Rapid Visual Information Processing, Multitasking test, and Spatial Working Memory, and the Auditory Verbal Learning Test [38]. This enabled an in-depth characterization of cognitive function, including measures of attention, visual perception, processing speed, verbal learning, memory, and executive functions, particularly working memory and inhibitory control. Lifestyle habits are screened with the Lifestyle Assessment Toolkit [39]. Physical activity habits are assessed with the International Physical Activity Questionnaire-Short Form [40].

The dementia risk score Lifestyle for Brain Health [41] is applied only at baseline to examine the presence of modifiable risk factors for dementia and, together with the measures International Physical Activity Questionnaire-Short Form, Geriatric Depression Scale, and the Lifestyle Assessment Toolkit, is used to examine potential moderators of program efficacy.

**Table T3:** **Table 3**. List of neuropsychological assessment measures used.

Number	Neuropsychological assessment protocol	Baseline	Postintervention
1	Informed consent and semistructured interview	✓	
2	Hand and eye laterality tests	✓	
3	Addenbrooke’s Cognitive Examination-Revised test	✓	✓
4	Geriatric Depression Scale	✓	✓
5	CANTAB^a^—Motor Screening Task	✓	✓
6	CANTAB—Rapid Visual Information Processing	✓	✓
7	CANTAB—Multitasking Test	✓	✓
8	CANTAB—Spatial Working Memory	✓	✓
9	Auditory Verbal Learning Test	✓	✓
10	Lifestyle for Brain Health (dementia risk score)	✓	
11	Reduced version of the Healthy Lifestyles Assessment Kit	✓	✓
12	International Physical Activity Questionnaire Portuguese Version (short)	✓	✓
13	Auditory Verbal Learning Test—long-term recall	✓	✓

a CANTAB: Cambridge Neuropsychological Testing Automated Battery.

### Assessment of Brain and Autonomic Function During Rest and Cognitive Task Performance

To examine the effect of the intervention on brain and autonomic function, we record the EEG, the pupilogram, and the ECG while participants are resting and while they are engaged in a value-based decision-making task (reinforcement learning task, described below). For the resting-state recording, participants sit in front of a computer screen and fixate on a target displayed at the center of the screen for 4 minutes.

#### Reinforcement Learning Task

A probabilistic reinforcement learning task adapted from Van Slooten et al [22] was designed using the Psychophysics Toolbox Version 3 [29,30] for MATLAB. The task consists of 2 main phases: learning and transfer (Figure 3). In the learning phase, 3 pairs of letters from the Latin alphabet (represented here as AB, CD, and EF) are associated with different reward probabilities (80%‐20%, 70%‐30%, and 60%‐40%). At the beginning of each trial, 2 letters appear at the horizontal meridian, left and right from the central fixation target, at 1.15° visual angle from the center of the screen. Participants choose 1 of the letters using the computer keyboard. The choice is highlighted by a small dark gray arrow pointing in the direction of the chosen option (Figure 3). After 1.5 seconds, the letters disappear, and auditory feedback is presented, indicating if the trial was rewarded or not. Auditory feedback consists of the spoken words in Portuguese: “one point” for rewarded trials, “zero points” for nonrewarded trials, or “no response” if the participant did not respond within the time window of 3.5 seconds. The intertrial interval is 3 seconds (from feedback onset to the start of the next trial). In the transfer phase, all 6 letters used are mixed to form 15 letter pairs (AB, AC, AD, AE, AF, BC, BD, BE, BF, CD, CE, CF, DE, DF, EF). Participants are asked to choose the letter with the highest reward based on previous learning. No feedback is provided during the transfer phase. Trials of the transfer phase follow the same trial structure as trials in the learning phase, except that no feedback is provided. Each session starts with a training block designed to explain the aims of the task, ensuring the participants understand the task rules and aims clearly. The learning phase consists of 4 runs and 90 trials per run, 360 trials in total. After each run, the number of points obtained is displayed. Directly after the learning phase, participants enter the transfer phase. The transfer phase consists of 3 runs and 60 trials per run, 180 trials in total. In the transfer phase, overall choice accuracy (percentage of times participants choose the letter associated with higher reward probability) is displayed only at the end of the recording session.

Participants are seated in a dimly lit room with their head positioned on a chin rest, 80 cm away from the computer screen. The letters (width × height=0.51° × 0.76° visual angle) are presented in a dark gray color on a lighter gray background (Figure 3). To minimize eye movements, participants are instructed to fixate on a fixation target displayed at the center of the screen throughout the whole task [42]. The luminance of the background, letters, and the fixation target are 47, 31, and 39 cd/m², respectively. Six different stimuli (6 letters) are randomly assigned for each participant and for each session (baseline and follow-up), corresponding to a total of 12 different letters assigned randomly for each participant.

**Figure 3. F3:**
[figure not shown]
Description of the reinforcement learning task used in the evaluation protocol. (A) During the learning phase, 1 of 3 letter pairs is presented in each trial. Participants choose one of the letters through key press. Each choice is followed by feedback indicating +1 point reward after a rewarded choice or no points for a nonrewarded choice. (B) The transfer phase evaluates how much was learned during the learning phase. All letters are randomly paired with one another, and participants are instructed to select the letter with higher value based on prior learning. Feedback is not presented in the transfer phase. (C) Reward probabilities of the 3 letter pairs used. (D) Value differences of the letter pairs used in the transfer phase.

#### EEG, ECG, and Eye Tracking Data Acquisition

A 64-channel Neuroscan system (Compumedics Europe GmbH) is used to measure EEG and ECG. The scalp electrodes are placed according to the International 10‐20 placement standard, with reference between the electrodes CPz and Cz and ground between FPz and Fz. The acquisition sampling rate is 500 Hz. Vertical and horizontal electrooculograms are recorded to monitor eye movements and blinks. Bipolar ECG electrodes are placed on the right shoulder and at the bottom of the sternum.

The EyeLink 1000 Plus desktop mount (SR Research) eye-tracking system is used to record the horizontal and vertical gaze positions and the pupilogram, with a sampling rate of 500 Hz. Eye position calibration and validation are run before each run. The participant’s head position is stabilized by using a chin rest to help reduce artifacts in the gaze signal that can be caused by head movements.

Trigger pulses are generated at the onset of each stimulus (letter pairs and auditory feedback) and at every button press.

### Adherence Rate and Adverse Events

Participants’ attendance is recorded for each exercise session. If a participant does not attend 2 consecutive exercise sessions, 1 researcher contacts the participant and encourages them to continue attending the classes. An adherence rate of 60% is necessary for inclusion in the analyses [43].

To ensure maximum safety, the following measures are taken: heart rate monitoring, performing exercise on a soft ground, and exclusion of participants with any health issue not compatible with moderate AE. Any adverse events that occur during the exercise program and study procedures are recorded by the researchers.

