### Study Design and Intervention Protocol

Our study consists of a 3-arm controlled trial with a parallel study design involving cognitively healthy older people. Participants are allocated into the Activ4Brain group and 2 control groups: an active control group engaged in AE alone and a passive control group, instructed to maintain their daily routines. The passive control group is included to control for the effect of test-retest. The AE group is included to assess if including cognitive training leads to a greater effect on cognition than AE alone and to control for the participants’ motivation to engage in the evaluation sessions, which might be decreased in passive control groups. The group allocation ratio is 1:1:1. The intervention consists of 24 sessions, held twice a week for 3 months. The participants are tested at baseline and after the 3-month training programs (Figure 1).

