### Study Outcomes

#### Assessment Procedures

Study outcomes are assessed at baseline and after the end of the intervention period (3-mo follow-up). Each assessment time point comprises 4 facility-based visits: (1) cognitive assessment (2 h), (2) EEG, pupil, and ECG recording session (2 h), (3) physical evaluation session (30 min), and (4) blood collection. Participants from the Activ4Brain group attend an additional visit to be assessed on the cognitive training tasks used in the program (30 min). The testing sessions end prematurely if the participants show signs of fatigue. Participants are informed of the preparation requirements, which will be checked prior to the assessments.

The study is designed to be powered for the primary outcome only (cognitive function). All secondary and other outcomes—brain and autonomic function (EEG, pupil, ECG), inflammatory and neuroprotective markers, physical fitness and body composition, feasibility and usability, and analyses of the associations between changes in these markers and changes in cognitive function—are exploratory. They are not individually powered and are intended to generate new hypotheses and inform the design of future, adequately powered studies.

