#### Secondary Outcomes

Secondary outcomes include:

Evaluation of the impact of the Activ4Brain program on brain and autonomic function and physical health markers, including molecular changes associated with inflammation and neuroprotection, and investigation of potential moderators of the program’s efficacyEvaluation of participants’ adherence and retention through attendance rates across all intervention sessions and participation trends over timeEvaluation of the feasibility of the Activ4Brain program, including its acceptability, accessibility, and usability

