### Statistical Analysis Plan

The study of the effect of the Activ4Brain program on the primary outcome (cognitive function) is confirmatory because we hypothesize, according to previous evidence, that the integrated cognitive-aerobic training program results in larger improvements than AE alone or no intervention (passive control) [47]. All other analyses are exploratory.

Continuous cognitive outcomes will be summarized descriptively with mean (SD) for each group and time. These variables will be analyzed with repeated-measures ANOVA with 1 between-subjects factor (group) and 1 within-subjects factor (time=preintervention vs postintervention). The Activ4Brain intervention will be considered effective in improving cognitive function if the group × time interaction is significant at a level of .05, if the post hoc tests (with CI adjustment using Bonferroni) show a significant effect of time for the Activ4Brain group, and the improvement is higher for this group than for the other control groups. If the data do not meet assumptions of sphericity, the Greenhouse-Geisser correction will be used. Description of the effect sizes by partial η^2^ will follow the following cutoff points: less than 0.06 will be considered a small effect; between 0.06 and 0.14 will be considered a medium effect; and higher than 0.14 will be considered a large effect [48].

Missing data will be assessed prior to analysis. Analyses will be conducted using the available data (complete case analysis), and participants with missing data for a specific outcome variable will be excluded only from the relevant analysis.

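### The 60% attendance rule is an unrestricted post-allocation exclusion that can remove people only from the two training arms, leaving the group × time test and the comparisons with passive control open to selection bias

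*Protocol article*

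**What the plan says.** Under Adherence Rate and Adverse Events the article says "Participants’ attendance is recorded for each exercise session" and then "An adherence rate of 60% is necessary for inclusion in the analyses". It does not say which analyses are meant and does not call the restricted set per-protocol or sensitivity.

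Under Study Design and Intervention Protocol, "The intervention consists of 24 sessions, held twice a week for 3 months", and the third arm is "a passive control group, instructed to maintain their daily routines". "The group allocation ratio is 1:1:1".

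The Statistical Analysis Plan section describes the primary test as confirmatory. It is a repeated-measures ANOVA with a group × time interaction at .05, followed by Bonferroni-adjusted post hoc tests. Success also needs a significant time effect in Activ4Brain and a larger improvement there than in the control groups. The only other rule on who is analysed is complete-case: "participants with missing data for a specific outcome variable will be excluded only from the relevant analysis". Nowhere does the article describe an analysis of all participants as allocated, and the limitations in the Discussion do not mention the attendance exclusion.

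**The concern.** Attendance is observed after allocation, and only in two of the three arms. Passive participants have no attendance rate, so the only workable reading is that all of them stay in. A trained participant who comes to 14 sessions is dropped, while a passive participant with the same motivation, health or free time is kept. The training arms are then a selected subset compared with an unselected group.

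If those who attend poorly would also have gained less on the cognitive tests, whatever the programme did, the retained training means are too high relative to passive control. The interaction test can then respond to selection rather than training. The sex and age balance built in under Randomization and Blinding is also no longer assured in the analysed set. The trial is quasi-randomized and unblinded, so it has little other protection.

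**Working it through.** **1. The threshold.** 0.60 × 24 = 14.4, so at least 15 of 24 sessions are needed.

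**2. Who can be excluded.** Activ4Brain: yes. AE: yes. Passive control: no, because there are no sessions to miss.

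**3. Shift against passive control.** The documents give neither an exclusion rate nor a correlation, so both are assumed. Let q be the share of a training arm excluded and r the correlation between propensity to attend and cognitive change. With a normal attendance propensity cut off at its q-quantile z, and no true effect of training, the retained mean change rises by r × φ(z)/(1 − q), in SDs of change.

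| q | φ(z) | r = 0.2 | r = 0.4 |
|---|---|---|---|
| 0.10 | 0.1755 | 0.039 | 0.078 |
| 0.25 | 0.3178 | 0.085 | 0.169 |

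For example, 0.4 × 0.3178/0.75 = 0.169. With r = 0 the shift is zero; with negative r the sign reverses.

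**4. Effect on the interaction test.** A null simulation used 20,000 runs, 25 per arm, and exclusions only in the two training arms. The nominal level is 0.05.

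| q | r | Shift (SDs of change) | Type I error |
|---|---|---|---|
| 0.10 | 0.3 | 0.058 | 0.053 |
| 0.20 | 0.3 | 0.105 | 0.063 |
| 0.20 | 0.5 | 0.175 | 0.086 |
| 0.30 | 0.5 | 0.248 | 0.121 |

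With r = 0 the rejection rate stayed between 0.050 and 0.054. The last two rows use a correlation above the 0.2–0.4 range in step 3 and show a more extreme case.

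**5. Activ4Brain versus AE.** If both arms lose the same share, the shifts cancel. At r = 0.3, losing 20% of Activ4Brain and 5% of AE gives +0.07 SD; the reverse gives −0.07 SD.

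**6. Comparison with the effect the trial was sized for.** The sample size section gives f = 0.25, α = 0.05, power 0.95, 3 groups, 2 measures and N = 66. The correlation between measures is not stated; assuming 0.5, λ = f² × N × 2/(1 − 0.5) = 0.0625 × 66 × 2/0.5 = 16.5. Power is then 0.9535 at 66 and 0.9436 at 63, so 66 reproduces. On change scores, f = √(16.5/66) = 0.5. If one arm differs from two equal arms, the difference is 0.5/√(2/9) = 1.06 SDs of change. A shift of 0.04–0.17 is about 4–16% of that (0.04/1.06 and 0.17/1.06).

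**The case against.** The strongest reply is that the Discussion singles out Activ4Brain against AE alone as the expectation to be treated as confirmatory. Both of those arms face the same rule. Success also requires greater improvement than in the control groups, so inflation against passive control alone cannot meet it. This stands as a limit on the damage. It does not remove the point, because the interaction test includes the passive arm and the rule may exclude different shares of the two training arms.

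Several stronger readings are tempting but not supported:

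- **That the results are biased towards training.** The documents give no reasons for non-attendance and no relation between attendance and cognitive change. The direction is plausible, not shown.
- **That the bias amounts to most of a realistic effect.** The documents supply no benchmark that small. Against the trial's own design effect the shift is modest.
- **That the rule leaves the trial too small.** 73 × 0.9 = 65.7 is the planned 66 to within rounding, and the article does not say whether its 10% allowance already covers poor attenders.
- **That complete-case deletion adds a tilt towards training.** The fatigue provision, "The testing sessions end prematurely if the participants show signs of fatigue", applies to every arm, and Table 3 lists the tests without declaring an order of administration.
- **That the adherence outcome is truncated by design.** The secondary outcome covers "adherence and retention through attendance rates across all intervention sessions", which makes it unlikely that poor attenders are meant to be left out of it. The wording needs clarifying, no more.

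The article also says the results will mainly generate hypotheses. That lowers the stakes, but it keeps the confirmatory label for the primary comparison.

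**Conclusion.** The point holds. As written, the plan restricts its confirmatory analysis by a post-allocation criterion that only the two training arms can fail. The interaction test and the training-versus-passive contrasts are liable to selection bias, probably in favour of training if poor attenders would have improved less.

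Under the assumed 10–25% exclusion and correlation of 0.2–0.4, the shift is about 0.04–0.17 SDs of change. It is zero if attendance is unrelated to cognitive change. At 10% exclusion and r = 0.3 the type I error barely moves. Activ4Brain versus AE is distorted only by unequal exclusion, in either direction. The sample size calculation is not at fault. The case for changing the rule is that it governs entry to the confirmatory test and can still be corrected at the analysis stage.

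**What to change.** Define the primary analysis as all allocated participants, in their allocated arm, regardless of attendance, using every available follow-up assessment. A likelihood-based mixed model would also keep participants whose follow-up is missing. Move the at-least-60% set to a labelled sensitivity analysis and report the number excluded by arm. State that adherence, retention and adverse events are computed on everyone allocated.

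The cost is a change of wording and one additional analysis set. The estimated effect may be somewhat smaller once poor attenders are included. Data collection ended in April 2025, so poor attenders can contribute follow-up data only if they were assessed then. The report should say how many were.

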### Exit Interviews

At follow-up, the AE and Activ4Brain groups respond to custom-made satisfaction questionnaires and system usability surveys [44-46]. These questionnaires and surveys include questions regarding suggestions for program improvement and scales regarding their perception of the impact of the program on their well-being and their satisfaction with the program.

### Study Outcomes

#### Assessment Procedures

Study outcomes are assessed at baseline and after the end of the intervention period (3-mo follow-up). Each assessment time point comprises 4 facility-based visits: (1) cognitive assessment (2 h), (2) EEG, pupil, and ECG recording session (2 h), (3) physical evaluation session (30 min), and (4) blood collection. Participants from the Activ4Brain group attend an additional visit to be assessed on the cognitive training tasks used in the program (30 min). The testing sessions end prematurely if the participants show signs of fatigue. Participants are informed of the preparation requirements, which will be checked prior to the assessments.

The study is designed to be powered for the primary outcome only (cognitive function). All secondary and other outcomes—brain and autonomic function (EEG, pupil, ECG), inflammatory and neuroprotective markers, physical fitness and body composition, feasibility and usability, and analyses of the associations between changes in these markers and changes in cognitive function—are exploratory. They are not individually powered and are intended to generate new hypotheses and inform the design of future, adequately powered studies.

